## Abstract

There is an alarming tide of cardiovascular and metabolic disease (CMD) sweeping across Africa. This may be a result of an increasingly urbanized lifestyle characterized by the growing consumption of processed and calorie-dense food, combined with physical inactivity and more sedentary behaviour. While the link between lifestyle and public health has been extensively studied in Caucasian and African American populations, few studies have been conducted in Africa. This paper describes the detailed methods for Phase 1 of the AWI-Gen study that were used to capture phenotype data and assess the associated risk factors and end points for CMD in persons over the age of 40 years in sub-Saharan Africa (SSA). We developed a population-based cross-sectional study of disease burden and phenotype in Africans, across six centres in SSA. These centres are in West Africa (Nanoro, Burkina Faso, and Navrongo, Ghana), in East Africa (Nairobi, Kenya) and in South Africa (Agincourt, Dikgale and Soweto). A total of 10,702 individuals between the ages of 40 and 60 years were recruited into the study across the six centres, plus an additional 1021 participants over the age of 60 years from the Agincourt centre. We collected socio-demographic, anthropometric, medical history, diet, physical activity, fat distribution and alcohol/tobacco consumption data from participants. Blood samples were collected for disease-related biomarker assays, and genomic DNA extraction for genome-wide association studies. Urine samples were collected to assess kidney function. The study provides base-line data for the development of a series of cohorts with a second wave of data collection in Phase 2 of the study. These data will provide valuable insights into the genetic and environmental influences on CMD on the African continent.

## Background

Sub-Saharan Africa (SSA) is in the throes of an epidemiological and health transition, described conceptually by the complex patterns of change in health and disease, and interactions with demographic, dietary, economic and social determinants and their consequences[1–3]. Many recent studies have focused largely on South Africa as a proxy for the region [4–9] but this approach can make it difficult to unpack precisely where countries within SSA lie on the spectrum of the transition. Recently, robust population-based data generated by INDEPTH (International Network for the Demographic Evaluation of Populations and Their Health in low- and middle-income countries) and its partners have provided insight into the extent to which SSA is experiencing an epidemiological change [10,11]. Examining 70,810 verbal autopsies (VA) from 80,880 deaths from 10 field centres across seven countries in the region, they provide some of the first empirical evidence from individual countries in SSA of increasing mortality because of non-communicable diseases (NCD). As an outcome measure for NCD, verbal autopsies have provided a powerful means to track whether countries within the region are achieving the goals set out by the World Health Organization (WHO) 25 × 25 targets. These include a 25% reduction in premature NCD mortality resulting from the four major NCDs (cardiovascular diseases, cancer, diabetes and chronic respiratory diseases) by 2025 [12], including a 25% relative reduction in prevalence of raised blood pressure, and aims to halt the rise in diabetes and obesity. However, complementary large-scale harmonized data on risk factor and morbidity burden, needed to address the latter target, are still lacking from Africa.

A number of studies aim to advance health in Africa through supporting research into healthy life trajectories. One study in South Africa focuses on reducing transgenerational risk of obesity and metabolic disease in the disadvantaged urban area of Soweto in Johannesburg, and is called ‘Building Knowledge and a Foundation for Healthy Life Trajectories in South Africa: A Preconception Developmental Origins of Health and Disease (DOHaD) Intervention Cohort’ [13,14]. The study represents a vulnerable population and is a community-based intervention study that aims to improve the health and well-being of disadvantaged women before and during pregnancy to improve health outcomes in their children. Other recent studies commissioned by *The Lancet* serve to underpin a necessary focus on understanding the determinants of healthy living in Africa [15,16].

In 2012 a new partnership between the University of the Witwatersrand (Wits) and INDEPTH, the AWI-Gen study (Africa Wits-INDEPTH partnership for Genomics studies), was formed. This study is funded by the National Institutes of Health as part of the Human Heredity and Health in Africa Consortium (H3Africa) [17,18]. AWI-Gen’s main purpose is to further understand the prevalence of cardiometabolic disease (CMD), associated risk factors, regional burden, and to explore gene–gene and gene–environment interactions that contribute to disease risk.

The conceptual framework for AWI-Gen (Figure 1) illustrates the different components of the study that will be explored to increase our understanding of the CMD outcomes in the different regions of SSA. Data on non-modifiable factors such as age, sex and genetic susceptibility to disease, and modifiable factors such as lifestyle, including diet and physical activity, and biomarkers of CMD including BMI, fat distribution, blood pressure and lipid profiles were collected at base-line in Phase 1 of the AWI-Gen study. AWI-Gen deliberately examines older adults aged between 40–60 years, a period during which CMD is most likely to present, and therefore enhances its ability to discover associations between CMD outcomes and risk factors, including genetic susceptibility. In line with the H3Africa mandate, there is a focus on assessing genomic associations with common diseases among Africans [17].

**Figure 1. F0001:**
[figure not shown]
Conceptual framework for Phase 1 of the AWI-Gen study. To begin to understand the cardiometabolic disease endpoints in the six sub-Saharan African communities, we collected data on non-modifiable biological factors and a host of mediators and potential confounders, including behavioural data and infection history and measures of body composition that include height, weight, waist and hip circumference (WC and HC), visceral and subcutaneous fat (VAT and SCAT) and carotid intima-media thickness (CIMT). Also measured were markers indicative of cardiometabolic disease (CMD) including blood pressure, glucose and insulin, urinary albumin protein and creatinine (UAPC) and serum creatinine (SC).

The AWI-Gen partnership leverages unique strengths of the INDEPTH health and demographic surveillance systems network [19] and the MRC/Wits Developmental Pathways for Health Research Unit (DPHRU) in Soweto, Johannesburg [20], to access established frameworks for population-based research. These include infrastructure for longitudinal and cross-sectional field research, experience in establishing community engagement and retention programmes, and facilities in which clinical history, medical examinations, and collection of blood and urine samples can be carried out. The AWI-Gen Collaborative Centre’s central hub at the Sydney Brenner Institute for Molecular Bioscience at the University of the Witwatersrand in Johannesburg, South Africa, also includes a biobank [21] and leads the genomic research with bioinformatics expertise. This, in turn, provides a foundation for training and capacity building for all its partners through a series of workshops and by hosting postgraduate students. AWI-Gen thus provides a research platform for data collection and aggregation with which to study the transitions in African health and disease risk. In our earlier publication [22] we described the AWI-Gen network and our plans to develop a research platform for epidemiology and genomic studies in SSA. In the current paper we describe the detailed methodology for data and sample collection, together with the quality control (QC) processes undertaken during Phase 1 of the AWI-Gen study.

## Methods

### Study setting

The African centres of the INDEPTH network were invited to participate in the study and five Health and Demographic Surveillance System (HDSS) sites responded. Fortuitously they covered West, East and South Africa and represented rural and urban settings. Six study centres in four SSA countries were involved in Phase 1 of the AWI-Gen study: in South Africa, the MRC/Wits Agincourt HDSS [23], Dikgale HDSS [24] and the Soweto centre located within the MRC/Wits Developmental Pathways for Health Research Unit [20]; in Kenya the African Population and Health Research Center HDSS in Nairobi [25]; in Ghana the Navrongo HDSS in the Navrongo Health Research Centre [26]; and in Burkina Faso the Nanoro HDSS hosted by the Institut de Recherche en Sciences de la Santé Clinical Research Unit [27]. The study is coordinated by the AWI-Gen Collaborative Centre based at the Sydney Brenner Institute for Molecular Bioscience, University of the Witwatersrand in Johannesburg, South Africa.

### Study design, participant inclusion and exclusion criteria

The AWI-Gen study [22] is a cross-sectional population study of 10,702 participants aged 40–60 years, recruited between August 2013 and August 2016, plus an additional 1021 participants over the age of 60 recruited at the Agincourt centre. Pregnant women, first-degree relatives of existing participants, recent immigrants (with less than 10 years of residence in the region) and individuals with physical impairments preventing measurement of blood pressure and other anthropometric indices were excluded from the study.

#### Details of sampling frames

Participants were selected via random sampling based on existing population sample frames from the respective research centres. For each of the Dikgale, Nairobi, Nanoro and Navrongo centres, participants were randomly selected until participant recruitment targets of approximately 2000 were attained, comprising similar numbers of women and men. There was some oversampling to account for non-responders and participants who did not meet study inclusion criteria. Various approaches were used in an attempt to remove bias as follows. In Nanoro there was a skewed age pyramid with more women than men, and so the sampling frame was adapted on a village by village basis to include equal numbers of randomly selected women and men. In the Navrongo region there was an uneven distribution of ethnolinguistic groups. To address this, a two-stage sampling frame was used: the west and east zones of the HDSS region were purposefully chosen, and then adults were randomly selected until roughly equal proportions of the two main ethnolinguistic groups (Kassena and Nankana), and a balanced gender ratio had been achieved. In Nairobi, participants were selected using a geographical sampling frame that covered the two peri-urban districts of Korogocho and Viwandani, until roughly equal numbers of female and male participants had been recruited from each district. In Dikgale, participants were selected randomly from a regional geographical sampling frame, but they were unable to reach recruitment targets, especially for men, before the end of the study period in 2016.

Sampling at the Agincourt HDSS in rural Mpumalanga was done from the 2013 population census by identifying all adults aged 40 and above as of 1 July 2014 and who were documented as permanently residing in the study area. Individuals who had participated in previous studies were invited to participate, and the numbers were randomly supplemented up to 2000 in the 40 to 60 year age range, stratified by sex to achieve equal numbers of women and men. Of these, 1465 individuals were successfully recruited into the study. In addition, 1021 individuals over the age of 60 years were recruited for data and sample collection according to the same protocol. Due to migration, the permanent population of the area has a bias in favour of women, and so gender-specific sampling fractions were developed in order to ensure a balance of women and men.

At the Soweto centre, based in Johannesburg, female participants between the ages of 40 and 60 years at the time of data collection were recruited from an existing cohort of caregivers called ‘Birth to 20 plus’ (BT20+) [20]. Approximately 700 of the women selected from this cohort were also part of the ‘Study of Women Entering and Endocrine Transition’ (SWEET) [28]. The remaining participants, including approximately 1000 men, were recruited through random selection using a geographical-based sampling frame that covered the Soweto region.

### Informed consent, ethical considerations and translation of documents

A broad consent process was adopted for the study [29,30] to promote the ethical use of the data and samples for future studies and to protect participants from potential harm. In the rural centres this was preceded by a process of community engagement involving assent from the community leaders.

All participants were provided with an information sheet, ‘Genomic and Environmental Risk Factors for Cardiometabolic Disease in Africans – Trait Association Study’ (see Supplementary Material 1), that described the study. Each individual was then asked to provided written informed consent. These documents were either in English or translated into the local language or dialect of the participant. For those participants who could not read or write, the documents were read in the presence of a witness, and an opportunity was provided to discuss their questions or concerns. It was the responsibility of the trained interviewer to ensure that any questions or objections raised during the consenting process were noted and appropriately addressed. Those who were unable to sign placed their thumb-print on the consent form to denote consent and this was witnessed and signed by a third party. One copy was archived at the local centre and the second given to the participant. The participant was then assigned a randomly generated participant AWI-Gen study ID that was used on all future data related to that participant to ensure protection of the participant’s anonymity. The coded ‘key’ to link participant personal identifying information with the AWI-Gen study ID was kept in a locked cabinet at the local centre and not disclosed to the AWI-Gen Collaborative Centre. All participant consent forms are kept at the individual centres and each centre provided a letter to the Collaborative Centre to confirm that appropriate consent was obtained for all the participants enrolled in the study.

Prospective participants were asked that prior to participating in the study, they refrain from eating or drinking (apart from water) from the night before to enable blood samples to be collected in the fasting state. They were also told that a urine sample would be requested, and were asked to bring any medication which they were currently taking for chronic illness. Participants were provided refreshments after the blood draw, and at some centres a cash reimbursement was provided to cover out-of-pocket expenses incurred by their visit.

Informed consent, information sheets and, in some cases, the questionnaire were translated into local languages when required, by well-trained staff of the centre who were fluent in both languages. The original English questionnaire was then compared to the translated version and discrepancies noted, discussed and resolved. During project training, each question was reviewed by the entire project team and discrepancies noted, discussed, and resolved with consensus. Documents were translated into the following languages: Shangaan (Agincourt), Spedi (Dikgale), Kishwali (Nairobi), French (Nanoro), Kasem and Nankam (Navrongo). No translations were necessary at the Soweto centre.

### Questionnaire design

#### Format

The participant questionnaire was designed using a REDCap (Research Electronic Data Capture) computer database [31,32]. This questionnaire was then transposed to a printable portable document format (PDF) and spacing minimized to generate a compact paper-based questionnaire. This paper questionnaire was then administered to participants at five of the centres. At the sixth centre, Agincourt, the questionnaires were administered in an electronic format using a tablet to facilitate harmonization of the data with another ongoing study – ‘Health and Ageing in Africa: A Longitudinal Study in an INDEPTH Community’ (HAALSI) [33].

#### Data capture and quality control (QC)

The responses to the paper-based questionnaires together with the anthropometry and ultrasound results were manually entered into a REDCap [31,32] computer database installed on a ‘Mac Mini’ computer that was located at each of the centres. Before transferring the data to the AWI-Gen Collaborative Centre, data clerks at each centre checked data for outliers and missing data according to their own internal data management and quality control processes, which included a check of 10% of all entries for consistency between the paper form and the electronic version. Agincourt electronic data was checked by the Agincourt data managers and converted to a form ready for export to REDCap.

Anonymized data were transferred through a secure File Transfer Protocol connection to the central REDCap server at the AWI-Gen Collaborative Centre, where the data was exported into a PostgreSQL database, and a second QC process was performed to search for outliers and missing data, which were then resolved by referring these records back to the local centres for further checks.

At the AWI-Gen Collaborative Centre, a total of 10% of all ultrasound scans were reviewed by a medically trained expert. Intra- and inter-observer differences were estimated by calculating the mean (and 95% confidence interval) of the arithmetic differences between measurements taken in the field and those during QC. The technical error of measurements was maintained at less than the 5% recommended maximum level, with no statistically significant differences observed (*p < *0.05) [34].

Once the data had passed all QC processes, a new version of the database was generated and ‘locked’ to prevent further changes. Data belonging to each centre was then returned for further rounds of QC to check accuracy of data entry and to correct any mistakes or inconsistencies, with each subsequent version of the database being assigned a unique version number and locked to prevent further change.

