#### Ultrasound measurements

A LOGIQ e ultrasound system (GE Healthcare, CT, USA) was used to measure visceral (VAT) and subcutaneous adipose tissue (SCAT), as well as carotid intima-media thickness (CIMT). A 2–5 MHz 3C-RS curved array transducer was used to measure both VAT and SCAT while a 12L-RS straight transducer was used to measure CIMT. To ensure consistency across all centres, selected researchers (including nurses, clinicians and researchers) from each site were trained centrally at the DPHRU in Soweto. The ultrasound examinations took approximately 30 minutes to complete and images and semi-automated measurements were recorded on a sample data collection sheet and transcribed to the paper questionnaire. Images were saved on a hard drive to prevent loss of data after examination, and periodically bulk-uploaded or transferred using a hard drive to the AWI-Gen Collaborative Centre server for archiving.

To capture VAT measurements, the ultrasound machine measurement was set to a depth of 15 cm and image to be captured labelled as ‘medial’. With the participant in the supine position, gel was applied to the lower abdomen and the probe positioned with minimal compression on the midline at a level midway between the lower costal margin and the iliac crest. The xiphi-sternum and umbilicus were used as a guide for accurate positioning. The spine was positioned horizontally, and the vertebra centrally in the image, and the gain setting adjusted accordingly. The participant was then asked to breathe quietly, and the measurement was taken at the end of the expiration. To calculate the amount of VAT, the paused ultrasound image was brought up onto the screen. The first cursor was placed anterior to the spine (on the fat pad if visible), and the second cursor on the thin peritoneal layer beneath the anterior rectus abdominus muscles. Care was taken to ensure that the measurement was perpendicular to the surface of the lumbar vertebra, and taken between the peritoneum and the spine, where there is a clear space between the vertebra and the aorta [47,48]. The measurement was repeated by producing a second image, and the results recorded in centimetres to two decimal places on a Sample Collection Data Sheet. The researcher did an immediate quality check to ensure that the spine, abdominal aorta and rectus abdominus muscle were visualized on the image.

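### The field-versus-QC ultrasound comparison cannot give intra-observer error, and a non-significant mean difference with technical error below 5% does not show agreement between centres

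*Protocol article*

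**What the plan says.** The section on data capture and quality control (QC) states that at the Collaborative Centre "a total of 10% of all ultrasound scans were reviewed by a medically trained expert". It then gives one method for differences both within and between observers, namely "calculating the mean (and 95% confidence interval) of the arithmetic differences between measurements taken in the field and those during QC". Two results follow. The first is "The technical error of measurements was maintained at less than the 5% recommended maximum level". The second is "with no statistically significant differences observed", with p < 0.05 in brackets, which is the threshold and not a result.

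The section on ultrasound measurements says who took the field readings: "selected researchers (including nurses, clinicians and researchers) from each site were trained centrally at the DPHRU in Soweto". For visceral fat (VAT) it adds "The measurement was repeated by producing a second image". Subcutaneous fat (SCAT) was also measured on a second image. For carotid intima-media thickness (CIMT) the left and right arteries were measured, with minimum, maximum and average recorded; no repeat reading of the same artery is described.

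The article does not say which pairs of readings gave the TEM, whether the differences were pooled or split by centre, or whether the duplicate VAT and SCAT values entered the intra-observer estimate.

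**The concern.** The stated calculation cannot produce one of the two quantities it is said to estimate. Intra-observer error needs the same observer to measure twice, and a field-minus-QC difference contains no such pair.

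The summary statistic is also weak for the purpose. A mean of signed differences measures average bias: positive and negative errors offset, and random error of any size leaves the expected mean at zero. Failing to reject a zero mean does not show that readings agree.

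The stake is comparison between centres. Each site used its own readers, so reader bias and centre are confounded. A systematic reading difference at one centre would look like a real difference in VAT, SCAT or CIMT. The article announces papers on body composition, plans longitudinal cohorts on this baseline, and claims cross-centre harmonisation in its conclusions. The QC statement is part of the support for that claim.

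**Working it through.** **Which pairs are compared.** Field reader: trained staff at the site. QC reader: a medically trained expert at the Collaborative Centre. Each difference d = field − QC therefore involves two readers. It carries inter-reader bias plus the random error of both. Same-observer error cannot be separated from it.

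**The article's own figure.** TEM below 5% and the non-significant test cannot be reproduced, because no differences, SDs, means or intervals are given. What follows tests what those two criteria would let through.

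**Inputs.**
- From the article: 10,702 participants aged 40–60, 10% of scans reviewed, TEM limit 5%, significance level 0.05.
- Derived: 0.10 × 10,702 ≈ 1,070 scan sets, assuming one set per participant and leaving out the Agincourt participants over 60.
- Assumed: differences pooled over six centres; half of the scans biased by +b and half by −b; random SD s of the difference. Both b and s are in % of the measurement mean.

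**Formulas.** Relative TEM = √(Σd² / 2n) / mean. Under these assumptions the expected mean difference is 0 and the expected d² is b² + s², so TEM ≈ √((b² + s²)/2).

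**Results** (share of significant tests from 4,000 simulated sets per row):

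| b | s | Mean difference | Tests significant | TEM | TEM < 5%? |
|---|---|---|---|---|---|
| ±3% | 5% | 0.0 | 2% | √(34/2) = 4.1% | passes |
| ±5% | 3% | 0.0 | 0% | √(34/2) = 4.1% | passes |
| ±10% | 5% | 0.0 | 0% | √(125/2) = 7.9% | fails |

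In the second row the pooled 95% CI is 0 ± 1.96 × √34 / √1,070 = 0 ± 0.35%. That looks precise and reassuring, yet a +5% centre and a −5% centre differ by 10%.

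**What the TEM limit bounds.** TEM = 5% means b² + s² = 2 × 25 = 50. With s = 0, the largest opposite bias that passes is √50 ≈ 7.1%. With s = 5%, it is √(50 − 25) = 5%. At TEM = 5% and zero mean, the 95% limits of agreement are ±1.96 × √50 ≈ ±13.9%.

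**If the analysis was by centre.** With 10% of 1,165 (Dikgale) to about 2,000 participants, each centre has about 117 to 200 QC scans. At s = 5%, the power to detect a 3% bias with n = 117 is Φ(3 / (5/√117) − 1.96) = Φ(4.53), above 99.9%. The test would then reveal the bias. TEM alone would not: a single centre with b = 5% and s = 3% also has TEM √(34/2) = 4.1%. The mean difference by centre is what separates the cases.

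**The case against.** The strongest reply is that agreement was not judged on the mean difference and the test alone. The TEM criterion squares the differences, so opposite errors do not cancel in it, and it would reject biases of ±10%. This stands. A reader might infer that the QC was blind to opposite biases of any size, and the article does not support that. The TEM narrows the problem to biases of roughly 5% to 7% or less under the assumptions above.

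Second, pooling over centres is not stated. A reader might infer that centre biases did cancel. The article neither says nor excludes this, and a condensed article may leave the level of analysis to a fuller procedure. If the test was run by centre, nothing cancels between centres. So the cancellation result is conditional only.

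Third, a reader might try to size the effect with CIMT biases of a few hundredths of a millimetre. CIMT was recorded in centimetres to two decimals, a step of 0.1 mm, so such biases lie below one recording unit, and rounding itself raises the TEM. The illustration is therefore kept in percent of the mean.

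Fourth, re-reading a stored image cannot detect differences in probe placement. That is true, but the QC section does not claim it does. Acquisition is addressed elsewhere through central training, landmarks and an immediate image check, so it is not counted here.

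Finally, duplicate VAT and SCAT images existed, and two analyses may have been compressed into one sentence. That is possible, but the sentence as written attributes both quantities to field-versus-QC differences. It also would not help CIMT, for which no repeat is described.

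**Conclusion.** Two points hold on the text alone. The field-versus-QC difference cannot estimate intra-observer error, although the article says it did. The absence of a significant difference is not evidence of agreement.

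A third holds conditionally. If differences were pooled over centres, the two stated criteria can both pass while two centres differ by 10% of the mean (biases of ±5%, random SD 3%, equal numbers of scans in each direction; all assumed). The article gives no SDs, so this shows what the criteria allow and says nothing about what happened. It does not establish that any centre was biased or that the ultrasound data are unreliable.

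**What to change.** 1. Estimate intra-observer error for VAT and SCAT from the two images taken per participant, provided that both values were kept and the same operator made both.
2. Withdraw the intra-observer claim for CIMT unless repeat readings by the same observer exist.
3. Describe the field-versus-QC comparison as inter-reader only, and say which readings gave the TEM and whether it was pooled.
4. From the existing QC readings, report by centre and by measure (VAT, SCAT, CIMT) the mean field-minus-QC difference with 95% CI, the 95% limits of agreement and the relative TEM. The mean difference by centre is essential, because TEM alone can pass a biased centre.
5. Drop non-significance as evidence of agreement.

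The cost is some re-analysis of stored readings. No new scans or readers are needed. The downside is that a centre may show a less favourable figure than the present overall statement.
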